### Recruitment and procedure

3.5

The recruitment will be conducted through advertisements and online platforms. Participants will be recruited from the Preventive Healthcare Center at the Affiliated Hospital of Chengdu University of Traditional Chinese Medicine. Recruitment efforts will involve posting posters in Preventive Healthcare Center and promotional content on the WeChat platform, outlining information such as the target patient population, eligibility criteria, interventions, and contact details. Participants will be provided study brochure and requested to fill up screening form. Patients will be required to sign a informed consent form if they meet the eligibility and agree to participate. Outcomes will be evaluated at baseline, 4 weeks (mid-intervention), 8 weeks (post-intervention), and follow-up period. In each group, 24 individuals will be selected for fNIRS scanning before and after intervention. Additionally, 24 healthy participants and 24 insomnia patients without cognitive impairment will be included as controls for assessing the brain functional characteristics of CID with MCI patients before intervention (Figure 1).

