## Data analysis

7

Data analysis will follow the intention-to-treat (ITT) strategy and will be conducted using IBM SPSS version 26.0 software (IBM Corp, New York). A *p*-value of ≤0.05 will be considered statistically significant. To address missing data, the Last Observation Carried Forward (LOCF) method will be employed for imputation. Continuous variables will be expressed as mean ± standard deviation, while categorical variables will be presented as numbers and percentages. Categorical variables will be analyzed using the Chi-Square Test. For continuous variables that follow a normal distribution, comparisons between groups will be made using an independent samples *t*-test, while paired samples *t*-tests will be used for pre- and post-treatment comparisons within the same group. For continuous data that do not follow a normal distribution, the Mann–Whitney U test will be used, with results expressed as the median and interquartile range. *p*-values obtained from the statistical tests, both for clinical outcomes and fNIRS data, will be corrected using the false discovery rate (FDR) method to account for multiple comparisons.

The raw fNIRS data will be preprocessed using NIRSPARK software, which includes format conversion, motion correction, artifact processing, and bandpass filtering. Data analysis will be performed using a dedicated module in MATLAB (R2020a).

Previous studies have demonstrated that patients with cognitive impairment due to insomnia exhibit working memory deficits correlated with cognitive performance, alongside altered connectivity patterns between the prefrontal and temporal regions (28). These findings suggest that these regions may constitute the neural basis of cognitive impairment in this population. Furthermore, acupuncture has been shown to modulate network connectivity within the prefrontal and temporal lobes in insomnia patients (29). Therefore, in this study, we will select the prefrontal and temporal regions as the regions of interest (ROIs) for activation and functional connectivity analyses. Visual representations will be generated to facilitate intuitive presentation.

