In MATLAB, the NIRS-SPM will be used for analysis, converting raw data into “.mat” format. The modified Beer–Lambert law will be applied to calculate blood oxygen concentration from the raw optical intensity data. The Topo-maker module will determine the optode configuration based on standard three-dimensional brain space positional information. Initial data checks will identify channels with potential abnormalities or noticeable noise, labeling them as bad channels.

To address physiological noise and head motion artifacts, temporal derivative distribution repair (TDDR) will be employed to remove spike artifacts and baseline shifts. Subsequently, a band-pass filter will be applied to eliminate noise from heartbeats, respiration, and Mayer waves, setting the filter range to 0.01–0.1 Hz according to the experimental paradigm.

For functional connectivity analysis, the data will be segmented into resting-state and task-state periods (0-back, 2-back). Connectivity measures, including correlation coefficients (corr), coherence (coh), and phase-locking values (PLV), will be calculated across all channels for each subject. Individual connectivity matrices will be constructed, and group-level averages will be computed for each condition. Statistical analyses, such as *t*-tests or ANOVA, will compare differences between conditions. The results will be visualized using connectivity matrices and brain network plots, and the findings will be interpreted in relation to cognitive function and task-related changes.

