Acupuncture, a widely used external therapy, offers advantages over pharmacological treatments, such as avoiding drug toxicity and side effects (48). The efficacy of acupuncture can be explained through various mechanisms, including modulating neurotransmitter release, reducing brain tissue inflammation, eliminating free radicals, inhibiting neuronal apoptosis, and suppressing tau protein expression. Recent studies have assessed the effectiveness of acupuncture (49, 50). Nevertheless, there is a debatable viewpoint suggesting that the efficacy of acupuncture may be primarily attributed to a placebo effect (51). In this study, the effectiveness of acupuncture will be assessed using placebo control to mitigate the non-specific effects of acupuncture. Concurrently, fNIRS will be utilize to investigate the functional characteristics of brain regions in patients, identify imaging characteristics associated with the disease. Compare characteristics before and after the intervention to explore the effect of acupuncture on modulating the function of these regions.

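### Section 7 names only the Mann–Whitney U test for non-normal continuous data and does not confine it to between-group comparisons, so as written it also falls on paired pre/post data

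*Protocol article*

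**What the plan says.** Section 7 (Data analysis) distinguishes two situations for normally distributed variables. Between arms: "For continuous variables that follow a normal distribution, comparisons between groups will be made using an independent samples" t-test. Within an arm: "paired samples *t*-tests will be used for pre- and post-treatment comparisons within the same group".

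The next sentence covers everything else: "For continuous data that do not follow a normal distribution, the Mann–Whitney U test will be used, with results expressed as the median and interquartile". It has no restriction to between-group comparisons. No signed-rank or other paired rank test appears anywhere in the article.

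The same paragraph applies its multiplicity correction to p-values "both for clinical outcomes and fNIRS data". Section 3.5 says of the imaging subset: "In each group, 24 individuals will be selected for fNIRS scanning before and after intervention". The Discussion states a before–after purpose for these data: "Compare characteristics before and after the intervention to explore the effect of acupuncture on modulating the function of these regions".

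**The concern.** A pre/post comparison asks whether the same person has changed. The Mann–Whitney U test derives its null distribution by treating the two sets of values as independent samples, so it ignores the pairing. When a person's two values are positively correlated, the test assumes more noise in the comparison than there is. Its actual error rate falls below 5%, and power falls with it.

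Section 7 recognises pairing for normal data and loses it for non-normal data. The outcome of a normality check would then change whether pairing is used at all, as well as how robust the test is. Two scales with the same true within-arm change could give different answers for that reason alone. The loss matters most where few people are measured twice, which here is the fNIRS subset.

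**Working it through.** **Inputs from the article.** 24 people per group scanned before and after (section 3.5). MoCA changes of 3.22 ± 1.88 and 1.97 ± 1.77 (section 3.3). The article gives no power figure for a within-group comparison, so there is none to reproduce.

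**Assumptions, not in the article.** Pre/post correlation r from 0.3 to 0.8; a moderate shift of 0.5 SD of the raw score; two-sided 5% level; skewed data.

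**Step 1: direction, by hand.** For a difference of two means, the independent-samples variance is 2σ²/n, while the true variance with pairing is 2σ²(1−r)/n. The unpaired statistic therefore has true standard deviation √(1−r) instead of 1. Under no change it rejects with probability 2[1−Φ(1.96/√(1−r))]:
- r = 0.3: 1.96/0.837 = 2.34, about 1.9%
- r = 0.5: 1.96/0.707 = 2.77, about 0.6%
- r = 0.7: 1.96/0.548 = 3.58, under 0.1%

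The error is conservative.

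**Step 2: power, by hand (means, n = 24, shift 0.5 SD).** The unpaired signal is 0.5/√(2/24) = 1.73. Unpaired power is Φ[(1.73−1.96)/√(1−r)]. Paired power is Φ[0.5/√(2(1−r)/24) − 1.96].
- r = 0.3: about 39% unpaired; Φ(2.07−1.96), about 54% paired
- r = 0.5: about 37% unpaired; Φ(2.45−1.96), about 69% paired
- r = 0.7: about 34% unpaired; Φ(3.16−1.96), about 88% paired

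**Step 3: the rank tests, by simulation.** Each value is a person effect plus an independent error, both standardised gamma with shape 2, combined to give correlation r. n = 24, raw shift 0.5 SD.

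| r | Mann–Whitney | Signed-rank |
|---|---|---|
| 0.3 | about 44% | about 54% |
| 0.5 | about 43% | about 70% |
| 0.7 | about 43% | about 88% |

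With no change, Mann–Whitney rejects about 0.5% of the time or less at r = 0.5 to 0.7, to within simulation error. Mann–Whitney power is roughly flat in r when the raw shift is held constant. The gap widens because the paired test gains.

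**Step 4: a different skewed model.** Lognormal data, n = 24, shift 0.5 SD on the log scale, Mann–Whitney versus signed-rank: 35% vs 43% (r = 0.3), 33% vs 55% (0.5), 31% vs 76% (0.7), 30% vs 90% (0.8). At r = 0 nothing is lost (37% vs 34%). Actual error rates of Mann–Whitney are 2.1%, 0.6%, 0.1% and near 0% at r = 0.3, 0.5, 0.7 and 0.8; the signed-rank test stays near 5%.

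**Step 5: MoCA-sized changes.** The cited changes are 3.22/1.88 = 1.71 and 1.97/1.77 = 1.11 SDs of the differences. In the gamma model with 37 to 45 people and r from 0.3 to 0.8, Mann–Whitney power is at least 99%. Nothing of practical importance is lost there.

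**The case against.** The strongest reply is that the sentence means between-group comparisons only. Mann–Whitney is the usual counterpart of the independent t-test, and the authors plainly know the paired/independent distinction. On that reading the article merely leaves a paired rank test unnamed, which a condensed article may do. The reading is possible, but the text does not express it: the rule is stated for non-normal continuous data in general, directly after the within-group comparison.

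Other points on that side stand and limit the concern:
- The randomised comparison is untouched. Mann–Whitney between arms on change scores is valid, and within-arm tests cannot establish a treatment effect in a placebo-controlled trial.
- The error does not create false positives.
- How often the rule would be triggered is unknown. For paired data the normality of the differences is what matters, and bounded or skewed scores can have near-symmetric differences. In the gamma model a Shapiro–Wilk test rejects the differences in only about 16–17% of samples at n = 24. The article does not say whether raw values or differences are checked.
- Correlation and effect size are assumed.

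A reader might also infer that the connectivity contrasts between rest, 0-back and 2-back are to be analysed as if from different people. The article does not support this: "Statistical analyses, such as *t*-tests or ANOVA, will compare differences between conditions" is illustrative, and both families include paired and repeated-measures forms. Nor does the article expressly send fNIRS before–after data to Mann–Whitney, since the only tests it names for connectivity are these.

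**Conclusion.** The rule for non-normal data is stated too broadly and, followed literally, puts an independent-samples test on planned paired comparisons. For a moderate within-arm change (0.5 SD) in 24 people, the cost against the signed-rank test is about 10 percentage points of power at r = 0.3, 27 at r = 0.5 and 45 at r = 0.7. These figures rest on an assumed correlation, an assumed effect size and a skewed data model; the loss disappears at zero correlation.

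It would be wrong to conclude that real changes will generally be missed, or that the primary outcome is at risk. The loss concerns moderate within-arm changes in data judged non-normal. The between-arm MoCA comparison is unaffected, and within-arm changes of the size cited for MoCA would be found by either test. This is a worthwhile correction to secondary analyses and does not threaten the trial's main conclusion.

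**What to change.** In section 7, restrict the Mann–Whitney U test to between-group comparisons, and state that pre/post comparisons within a group use the Wilcoxon signed-rank test when the paired differences are not normally distributed. Naming the differences as the quantity to be checked also settles when the rule applies.

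The cost is one clause, with no extra participants or data. The only statistical downside is that the signed-rank test assumes roughly symmetric differences.

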**Methods and design:**

This study is a single-center randomized controlled trial. Participants will be randomly assigned to the manual acupuncture group or the placebo acupuncture group for an 8-week intervention period. fNIRS data will be collected during resting test and working memory test at baseline and at end of the intervention. The primary outcome is the change of the Montreal Cognitive Assessment (MoCA) score, secondary outcomes include the change of Mini-Mental State Examination (MMSE), Insomnia Severity Index (ISI), Patient Health Questionnaire-9 (PHQ-9), Generalized Anxiety Disorder Scale (GAD-7), and Apathy Evaluation Scale-Informant (AES-I).

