### Sample size calculation

3.3

According to a prior clinical study (32), sample size estimation is based on the Montreal Cognitive Assessment (MoCA) score. The differences in MoCA scores before and after treatment was (3.22 ± 1.88) for the acupuncture group and (1.97 ± 1.77) for the placebo acupuncture group. In the formula, with *α* = 0.05, *β* = 0.10, and k = 1, a sample size of 37 cases per group was calculated. Considering a dropout rate of 20%, we determined a sample size of 45 cases per group. Consequently, the total number of cases in both groups will be 90.

Using brain imaging data as an indicator of acupuncture-related studies, the sample typically ranged from 10 to 25 individuals per group (33–35). Thus, we will enroll at least 20 participants per group in fNIRS scanning. Considering a dropout rate of 20%, we determined a sample size of 24 cases per group.
$$n=\frac{{\left(u_{\alpha }+\mu_{\beta }\right)}^{2}\left(1+1∕k\right)\sigma^{2}}{\delta^{2}}$$

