## Outcome measures

5

Each participant will be evaluated by a medical professional blinded to the group assignment and intervention. Assessments will occur at five time points: baseline, 4 weeks, 8 weeks, 12 weeks, and 20 weeks. The schedule of this study is listed in Table 3.

**Table 3 tab3:** Study schedule.

Timepoint	Enrolment	Baseline	Treatment phase		Follow-up phase	
	1 week	0 week	4 weeks	8 weeks	1 month	3 months
Enrolment						
Eligibility screen	**×**					
Medical history	**×**					
Informed consent		**×**				
Allocation		**×**				
Interventions						
Manual acupuncture		**×**	**×**	**×**		
Placebo acupuncture		**×**	**×**	**×**		
Health education		**×**	**×**	**×**		
Assessments						
Demographics	**×**					
fNIRS scanning		**×**		**×**		
PSQI	**×**	**×**				
MoCA	**×**	**×**	**×**	**×**	**×**	**×**
ISI		**×**	**×**	**×**	**×**	**×**
MMSE		**×**	**×**	**×**	**×**	**×**
PHQ-7		**×**	**×**	**×**	**×**	**×**
GAD		**×**	**×**	**×**	**×**	**×**
AES		**×**	**×**	**×**	**×**	**×**
SF-12		**×**	**×**	**×**	**×**	**×**
Safety assessment		**×**	**×**	**×**		
Vital sign		**×**	**×**	**×**		
Use of sleep medications		**×**	**×**	**×**	**×**	**×**

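### The FDR rule does not exempt the sole primary outcome, MoCA change, although the trial is sized for one unadjusted MoCA test; the stated power does not describe the planned primary analysis

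*Protocol article*

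**What the plan says.** Three parts of the protocol article bear on this.

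- **Primary outcome.** The abstract states: "The primary outcome is the change of the Montreal Cognitive Assessment (MoCA) score". Section 5.1 lists MoCA alone under the primary heading.
- **Sample size (section 3.3).** The inputs are MoCA changes from an earlier study: "The differences in MoCA scores before and after treatment was (3.22 ± 1.88) for the acupuncture group". For the comparison arm the figures are "1.97 ± 1.77) for the placebo acupuncture group". The calculation is given as "with *α* = 0.05, *β* = 0.10, and k = 1, a sample size of 37 cases per group was calculated", followed by "Considering a dropout rate of 20%, we determined a sample size of 45 cases per group". It makes no allowance for multiplicity.
- **Analysis (section 7).** Significance is set at p ≤ 0.05. The section then adds that p-values, "both for clinical outcomes and fNIRS data, will be corrected using the false discovery rate (FDR) method to account for multiple comparisons". It does not set the primary outcome apart, and it does not say which tests form a family.

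The number of tests that could enter is large. Section 5 says: "Assessments will occur at five time points: baseline, 4 weeks, 8 weeks, 12 weeks, and 20 weeks". Table 3 schedules seven scales at the four post-baseline visits (MoCA, MMSE, ISI, PHQ, GAD, AES, SF-12). For fNIRS, correlation, coherence and "phase-locking values (PLV), will be calculated across all channels for each subject", with 43 channels.

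**The concern.** A sample size for one test at 0.05 and an analysis that adjusts that test for a list of others are two different procedures. Under Benjamini–Hochberg (BH), the usual FDR method, the cut-off for any one p-value is 0.05 × k/m, where m is the number of tests in the family and k the number rejected. Two trials with the same MoCA p-value of, say, 0.02 could therefore reach opposite conclusions on the primary outcome because MMSE, anxiety or quality-of-life results differ. The 90% power in section 3.3 is the power of a test with a fixed cut-off of 0.05, which is not the test that section 7 describes.

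This is more than detail left to an analysis plan. The article states a multiplicity rule, and an analysis plan that tested MoCA unadjusted would depart from that rule as written. Because the family is also undefined, the choice of family could decide whether the primary result counts as significant.

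**Working it through.** **Inputs from section 3.3.** Difference 3.22 − 1.97 = 1.25. Pooled SD = √[(1.88² + 1.77²)/2] = √3.3337 = 1.826. Alpha 0.05, power 0.90, allocation 1:1.

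**Reproducing the plan's own figure.** The formula is n = (u_α + u_β)² × 2σ²/δ².

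- One-sided alpha: (1.645 + 1.282)² × 2 × 3.3337/1.5625 = 36.5, so 37. This matches the protocol.
- Two-sided alpha: (1.960 + 1.282)² × 2 × 3.3337/1.5625 = 44.8, so 45. This does not match.

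So 37 per group gives 90% only for a one-sided test, and sidedness is not stated. That is a separate matter. It means that the two-sided starting point is already below 90% before any FDR correction.

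**Unadjusted power at 37 per group, two-sided.** The standard error is 1.826 × √(2/37) = 0.4245 and the standardised effect is 1.25/0.4245 = 2.945. Power = Φ(2.945 − 1.960) = 83.8% (82.8% with the noncentral t distribution).

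**Limiting case under BH: MoCA is the only real effect.** The cut-off for MoCA is then close to 0.05/m.

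- Seven scales at one visit, m = 7: cut-off 0.00714, z = 2.690, power Φ(0.255) = 60%.
- Seven scales at four visits, m = 28: cut-off 0.00179, z = 3.124, power Φ(−0.179) = 43%.

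These use the normal approximation; the noncentral t gives 57% and 39%.

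**BH by simulation, clinical outcomes only.** Settings: q = 0.05, two-sided normal tests, correlation between tests of 0 or 0.4, other real effects as strong as MoCA, 37 evaluable per group.

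| Tests in family | No other effect real | Half real | All real |
|---|---|---|---|
| 7 | 61% | 74–75% | 80–82% |
| 28 | 43–44% | 71–74% | 79–82% |

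With 45 per group and no loss of information, unadjusted two-sided power is 90.1%. The corresponding rows are 71%, 83–85%, 88–89% (7 tests) and 55–56%, 82–84%, 88–89% (28 tests).

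**Type I error of the MoCA test under the same rule.** With 37 per group it ran from 0.002 to 0.043 in these clinical families. It cannot exceed 0.05, because a BH-adjusted p-value is never smaller than the raw one.

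**If fNIRS tests shared the family.** There are 43 × 42/2 = 903 channel pairs. Adding one test per pair to the 28 clinical tests gives m = 931, and power in the limiting case is about 15%. With three metrics and three states, 903 × 9 + 28 = 8,155 tests, and it is about 6% (about 4% with the noncentral t).

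**The case against.** **The error rate.** A reader might infer that the 5% error rate no longer applies to MoCA, or that pooling with within-group pre/post tests, which may nearly all reject, lets false claims through. For a single MoCA comparison the documents do not support this. Suppose 28 null between-group tests are pooled with 56 within-group tests that all reject. The cut-off relaxes only to about 0.034, and the error for any one null test is about 3.4%. At least one of the 28 rejects in about 62% of such trials, but that is a statement about the whole list. The same 28 independent tests with no correction would give 1 − 0.95²⁸ = 76%. The scenario also assumes that every within-group test rejects, which no section states.

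**One pooled family.** A reader might also infer that MoCA is corrected together with thousands of fNIRS tests. The sentence in section 7 fits two separate families equally well, the software differs (SPSS for the main analysis, a MATLAB module for fNIRS), and section 3.5 limits scanning to 24 per group. The very low power figures therefore cannot be presented as what the plan does.

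**The power loss is a worst case.** This stands in part. MMSE covers the same domain as MoCA and ISI measures the treated condition, so some other effects may well be real if MoCA's is, and the loss is then much smaller. Section 7 also specifies intention to treat with last observation carried forward, so up to 45 per group may be analysed. But power still varies with other outcomes' results, and is still below that of the unadjusted test.

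**Visit and status.** Section 3.3 speaks of change from before to after treatment and section 3.5 labels week 8 as post-intervention, so week 8 is the natural reading and counting MoCA four times is an assumption. Section 9.1 calls the study exploratory. Neither point removes the mismatch: a single-visit family of seven scales shows it, and the trial still names one primary outcome and sizes for it.

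**Conclusion.** The point holds as a conflict between sections 3.3 and 7. The sole primary outcome is not exempted from FDR, while the sample size assumes one unadjusted test. This is so even if the clinical outcomes form their own family.

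The consequence is lost power and a cut-off for the primary test that depends on other results. It is not an inflated error rate for MoCA. With 37 evaluable per group, the cost against the unadjusted 83–84% runs from a few percentage points (all other clinical effects equally strong) to about 23 points with 7 tests or 40 points with 28 (no other real effect). The gap between 90% and 83–84% comes from the unstated sidedness, not from FDR.

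These sizes rest on assumptions that the document does not fix: BH as the FDR method, the test counts, two-sided testing, the pattern and strength of other effects, and correlations of 0 or 0.4. The direction of the loss does not depend on the exact counts, provided other tests share MoCA's family. Losses beyond this range would need fNIRS tests in the same family, which the text does not establish.

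**What to change.** In section 7, state the following:

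1. The between-arm difference in MoCA change at week 8 (post-intervention) is the single primary test, carried out alone at 0.05 outside any FDR family. State whether it is two-sided, so that it agrees with section 3.3.
2. FDR is applied separately to the between-arm secondary clinical outcomes and to the fNIRS tests, with the content of each family listed.
3. Within-group pre/post tests stay out of these families. They do not compare the arms, and they would otherwise move the cut-off for tests that do.

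This costs about one paragraph and no new data, and section 8 already provides the route for a change. It should be settled before unblinding. The price is that MoCA at weeks 4, 12 and 20 becomes secondary. Which fNIRS measure, if any, to single out as key is a choice for the investigators, and this point does not depend on it.
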